   1. PRIMARY OUTCOME

The primary endpoint of the study is the sufficient study participation to determine the representativeness of results for first, regular and full responders (compare figure 3).

[figure not shown]

*Figure 3: Overview of patient and participant segmentation*

As expected, study participation will vary depending on gender, age, and diagnosis, but this can be compensated for by weighting the study participants according to structural information on the target population. Within our study, data on healthcare utilization is available for participants and the whole BARMER population. Weighted measures of health care utilization from participants will be compared with measures of health care utilization of the complete target and will be assumed to be formally representative if the weighted measures from participants fall within the 95% confidence interval of the same measures based on data of the complete target population.

- 1. SECONDARY PARAMETERS OUTCOMES

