   1. GENERAL METHODOLOGY

Quantitative variables will be described as mean (respectively median), standard deviation (inter-quartile range), number, and rate of missing data, and compared between arms with a t-test, or if not appropriate with a Wilcoxon rank-sum test. Qualitative variables will be reported as absolute and relative frequencies, number, and rate of missing variables, and compared between sub-cohorts with the Chi-square test or the Fisher’s exact test. Variables will be compared between both sub-cohorts (DMP and non-DMP participants). P-value <0,05 with a bilateral hypothesis will be considered significant. All the analyses will be carried out using R, SAS, and other statistical software for Windows.

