**Primary Outcomes**

*Sufficient response rates for representativity of subgroups*

As expected, study participation will vary depending on gender, age, diagnosis, and healthcare utilization, but this can be compensated for by weighting the study participants according to structural information on the target population.

Within our study, data on the above-mentioned patient characteristics is available for both participants and the whole target population. Weighted measures from participants will be compared with measures of the complete target and will be assumed to be formally representative if the weighted measures from participants fall within the 95% confidence interval of the same measures based on data of the complete target population.

The general methodology (see 5.1) will be applied for the analysis of the primary outcomes.

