**Data analysis**

- Check for normality using the Shapiro–Wilk test
- Check for intraclass correlation using intraclass correlation coefficients
- Analyze missing data
- Descriptive statistics of patient and treatment characteristics
- Time series analysis
- Parametric and non-parametric methods
- Statistical tests depending on normality for the primary and secondary outcomes to compare:
  - Responders vs. non-responders (to the nudge)
  - DMP vs non-DMP members
- Linear and logistic regressions controlling for:
  - Significant patient characteristics
  - Significant other collected variables depending on the research question

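### Sections 4.1 and 5.2 define the primary representativeness check differently, and no rule turns several measures and three responder segments into a conclusion

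*Protocol*

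**What the plan says.** Section 4.1 states the primary endpoint as "sufficient study participation to determine the representativeness of results for first, regular and full responders". It says that "study participation will vary depending on gender, age, and diagnosis, but this can be compensated for by weighting the study participants", and then that "Weighted measures of health care utilization from participants will be compared with measures of health care utilization of the complete target" population. The measures "will be assumed to be formally representative if the weighted measures from participants fall within the 95% confidence interval of the same measures" in that population. No individual utilization measure, unit or period is given.

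Section 5.2 restates the endpoint under the heading "Sufficient response rates for representativity of subgroups". Its list of factors that weighting compensates for is gender, age, diagnosis and also healthcare utilization. It then refers back to those same characteristics as the data available for participants and target, and repeats the confidence interval rule for unspecified measures. It closes with "The general methodology (see 5.1) will be applied for the analysis of the primary outcomes". Section 5.1 says "Variables will be compared between both sub-cohorts (DMP and non-DMP participants"), with two-sided significance at 0.05.

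The data analysis list at the end of Section 5.2 adds "Statistical tests depending on normality for the primary and secondary outcomes to compare" two pairs: responders and non-responders to the nudge, and DMP and non-DMP members.

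Section 4.2 lists how representative responders are over time as a secondary outcome, although regular and full responders already stand in the primary endpoint of Section 4.1.

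**The concern.** The primary endpoint is meant to answer whether digital PROMs and PREMs can serve quality measurement at health-system level. For that, the protocol needs one comparison of participants with the target population and one way to read the result. It gives two versions that differ in the weighting factors, the quantity compared and the level of assessment, and it attaches tests with a different purpose. If utilization is both weighted on and checked, a pass says little. If utilization is only checked, a pass is informative. A reader of the final report could not tell from the protocol which of these was planned, or whether one measure outside its interval in one segment overturns the conclusion.

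**Working it through.** **Step 1. The two definitions side by side**

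| Element | Section 4.1 | Section 5.2 |
|---|---|---|
| Factors that weighting compensates for | gender, age, diagnosis | gender, age, diagnosis, utilization |
| Quantity compared | utilization, no measure named | the characteristics in the row above |
| Level | first, regular, full responders | subgroups, not listed there |
| Further method | none | Section 5.1 tests, DMP vs non-DMP |
| Rule per measure | inside the target's 95% interval | the same |
| Rule for combining measures or segments | none | none |

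Only the rule for a single measure agrees.

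**Step 2. Checking a variable that was used for weighting**

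Let a category of utilization have share p in the target and s among participants. Weighting to the target gives weight p/s inside the category and (1 − p)/(1 − s) outside it. The weighted share among participants is

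s × (p/s) / [s × (p/s) + (1 − s) × (1 − p)/(1 − s)] = p / [p + (1 − p)] = p.

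The weighted value equals the target value, which is the centre of the target's interval, whatever s was. The check passes for any participation pattern. This is exact when the same categories are weighted and checked. It is approximate when a coarse grouping is weighted and a finer measure, such as number of visits, is checked. The same holds for gender, age and diagnosis, which Section 5.2 also places among the compared characteristics. Under Section 4.1, where utilization is not in the weights, the check can fail.

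**Step 3. The added contrasts**

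Section 3 performs all analyses on patients who took part. DMP versus non-DMP among them compares one group of participants with another. The PRO feedback goes only to people who have already answered the first questions (Sections 2.4 and 2.6), so responders and non-responders to it are participants too. Neither contrast contains the target population. Both groups could be alike and unrepresentative, or different and jointly representative after weighting.

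**Step 4. The only participation figure**

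Section 2.5: 200,000 × 0.30 = 60,000 react; 60,000 × 2/3 = 40,000 allow follow-up; 40,000 × 0.40 = 16,000 with complete data. The stated 16,000 is reproduced. It is not tied to the representativeness rule, and no number of regular responders can be derived.

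**Step 5. Effect of the missing combination rule (illustration only)**

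Suppose k independent measures, each inside its interval with probability 0.95 when participants are truly representative.

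- All must pass: P(at least one outside) = 1 − 0.95^k. For k = 3: 1 − 0.857 = 14%. For k = 12: 1 − 0.540 = 46%.
- Any one suffices: P(failure) = 0.05^k, practically zero for k = 12.

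The value 12 is the number of service categories in Section 5.3. Those are secondary analyses and are not linked to the primary rule.

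**The case against.** The strongest reply is that much of this belongs in a statistical analysis plan, which may exist: naming measures, ordering segments, handling multiplicity. That stands for the names alone. It does not remove the conflict, because an analysis plan can follow Section 4.1 or Section 5.2 on weighting and compared quantities only by overriding the other. Nor can it be said from the protocol that the choice will be made after seeing the data.

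Second, the rule can be read measure by measure, and first, regular and full responders may properly receive three separate answers. That is a fair reading, and different answers by segment would then be results, not contradictions. The protocol would still need to say so and to say which answer carries the main research question. The reading in which any one passing measure is enough has no positive support in the text; it is merely not excluded.

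Third, the reference to Section 5.1 and the data analysis list may be loose cross-referencing, and Section 1.1 does ask how response rates vary by DMP participation. DMP comparisons of response rates therefore have a place. Nothing says that a DMP p-value decides representativeness, but the wording applies these tests to the primary outcome without limiting their role.

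A reader might infer that the plan rejects truly representative participants at some computable multiple of a nominal 5%. The documents do not support this. The number of measures, their correlation and the size of the regular-responder segment are not given, and a 5% failure chance per check is not a property of the stated rule. The interval is the target population's, so its width depends on a population size that is not stated. With an assumed target of 200,000 to 2,000,000, a simple random sample of 16,000 would fall inside for one measure with probability about 0.44 to 0.14. That is a separate matter of how the interval is built.

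**Conclusion.** The concern holds as an inconsistency in the definition of the primary endpoint. Sections 4.1 and 5.2 differ on the factors weighted, the quantities compared and the level of assessment. Section 5.2 also attaches contrasts among participants that cannot test representativeness against the target. Where utilization is both weighted on and checked, the check is close to uninformative. This rests on reading the factor list in Section 5.2 as the weighting variables, which is its plain sense. With no combination rule, opposite conclusions from the same data are both compatible with the text.

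No trial-specific error rate follows. The 46% above shows only how far the all-must-pass reading can move with 12 independent checks at an assumed 95% each. The conclusion does not depend on that number: with more than one measure, the readings can disagree.

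**What to change.** Use one identical definition in Sections 4.1 and 5.2:

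- Weight on gender, age and diagnosis only, and keep utilization out of the weights if it is the check. Section 2.5 names utilization among the criteria for drawing the sample. Weights that merely undo known invitation probabilities are a different matter and should be described separately.
- Name the deciding utilization measure, with unit and period. The choice is the sponsor's; total cost per patient-year is one example. Alternatively, give a short list with an explicit all-must-pass rule.
- Name the deciding responder segment and report the others as separate or ordered results. Bring Section 4.2 into line on whether representativeness over time is primary or secondary.
- Label all other measures and subgroups as descriptive.
- Replace the closing reference to Section 5.1 and limit the data analysis list, stating that the DMP versus non-DMP and nudge-responder tests do not decide the primary outcome. DMP comparisons of response rates stay as secondary outcomes.

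The cost is wording in Sections 4.1, 4.2 and 5.2, with no new data. The downside is that the formal conclusion covers fewer measures, and a single summary such as total cost can hide offsetting differences between types of care. The descriptive results should therefore be reported beside it.

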**For the primary research question:**

As secondary outcome for the primary research question, (1) the response rates overall and per patient subgroups based on disease area, patient characteristics (gender, age, disease), DMP participation, and others as well as (2) the representativity of responding participants over time. For these analyses, the study population is segmented in:

- All patients: Full BARMER-insured population with at least one of the chronic diseases included in the study
- Invited patients (from “All patients”): Patients that receive the initial invitation letter
- First responders (from “Invited patients”): Patients that complete the first survey period
- Regular responders (from “First responders”): Patients that complete at least three out of four survey periods
- Full responders (from “Regular responders”): Patients that complete all four quarterly survey periods

Variables that will be analyzed in all segments:

- Age
- Gender
- Type of chronic disease
- DMP participation

For all responder groups, additional variables from survey data will be analyzed:

- Body-Mass-Index (BMI), calculated by height & weight
- Education
- Profession
- Household size
- Household income

**For the second research question:**

- Share of low-value care (see Statistical Analyses section)
- Share of high-value care (see Statistical Analyses section)
- Outcome and patient experience variation across subgroups
- Adverse events such as hospital admission due to chronic disease profile

**For the third research question:**

- Comprehensibility of PRO feedback
- Helpfulness of PRO feedback
- Impact of PRO feedback on healthcare behavior overall and per subdimension
  1. OTHER PARAMETERS

**Demography and Baseline**

See Secondary Parameter Outcomes in 4.2.

**Safety**

Not applicable

**Laboratory**

Not applicable

1. Statistical Methodology
   1. GENERAL METHODOLOGY

Quantitative variables will be described as mean (respectively median), standard deviation (inter-quartile range), number, and rate of missing data, and compared between arms with a t-test, or if not appropriate with a Wilcoxon rank-sum test. Qualitative variables will be reported as absolute and relative frequencies, number, and rate of missing variables, and compared between sub-cohorts with the Chi-square test or the Fisher’s exact test. Variables will be compared between both sub-cohorts (DMP and non-DMP participants). P-value <0,05 with a bilateral hypothesis will be considered significant. All the analyses will be carried out using R, SAS, and other statistical software for Windows.

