**Subgroup analysis**

Subgroup analyses will be conducted by all patient characteristic variables under 4.2. Height & weight will be combined to BMI according to WHO standards. Additionally, subgroup analyses will be performed by DMP membership and healthcare utilization. Subgroup analyses cover all study participants as well as analyses of each chronic disease population.

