Based on the combination of PROMs, PREMs and health care system utilization measured as costs, a value-based healthcare cube is introduced. PROM and PREM scores function as outcome dimensions and healthcare system utilization as cost dimension. Costs are hence added as new axis inside the framework (see Figure 5).

[figure not shown]

*Figure 5: Assessment of Value-Based Healthcare - Framework*

The newly introduced value-based healthcare cube allows the measurement of high-value and low-value care. Along the previously defined areas of suspected high- and low-value care (see Figure 4 and 5), the cube can be subdivided into 27 segments (see Figure 6). High-value and low-value care will be investigated based on the following criteria:

- High-value indication in both dimensions (high patient-relevant indicators (PROMs/PREMs) **at** low costs) (Figure 6 – dark green area)
- High-value indication in at least one dimension (high patient-relevant indicators (PROMs/PREMs) **or** low costs) (Figure 6 – light green area)
- Low-value indication in at least one dimension (low patient-relevant indicators (PROMs/PREMs) **or** high costs) (Figure 6 – light red area)
- Low-value indication in both dimensions (low patient-relevant indicators (PROMs/PREMs) **at** high costs) (Figure 6 – dark red area)

The value of care dimensions will be summarized into high- versus low-value care as the broad definition and into high two-sided, high one-sided, low one-sided and low two-sided value care as narrow definition. For both categorizations the frequency as well as the variation per subgroups (e.g. region, DMP etc.) will be analyzed.

[figure not shown]

*Figure 6: Assessment of Value-Based Healthcare – Framework distinguishing between high- and low-value care*

*Outcome and experience variation*

Mean change in PROM and PREM-index (sub-)scores overall and per subgroup (see 5.1 and 4.3) per disease area over time:

- Average per survey period
- Consistency over time (test-retest reliability)

Meaningful change / Minimally clinical important difference (MCID) in PROM index (sub-)scores overall and per subgroup (see 5.1 and 4.3) per disease area over time:

- Average per survey period
- Consistency over time (test-retest reliability)

*Hospital admission risk based on PROMs/PREMs and patient characteristics*

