- Using machine learning predictive models (long-short-term memory deep learning network for time trend classification, random forest, logistic regression, decision tree and/or support vector machine) to identify admission risk in Q3 and Q4 based on PROMs/PREMs in Q1 and Q2

*PRO feedback*

- Mainly: Statistically significant change in at least one of the health care behavior dimensions (see 4.2) and comparison of participants who opened the report vs. those who did not, using logistic regression (change/no change)
  - Physical activity: Shift of participants to a higher category
  - Nutrition: Shift of participants to “More healthy” from any other category
  - Tobacco: Shift of participants to a lower category
  - Alcohol: Shift of participants to a lower category
  - Sleep: Share of stable participants (no significant variation in sleep duration)
- Secondly: Descriptive exploratory analysis of the rates of the following two evaluation dimensions and statistically significant differences in subgroups (see 5.1 and 4.3):
  - Understandability
  - Helpfulness
  - Emotional change

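### Section 5.1 calls any two-sided p<0.05 significant without saying which of the many DMP, disease-specific and subgroup comparisons the rule governs

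*Protocol*

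**What the plan says.** Section 5.1 (General Methodology) describes the tests and then gives one threshold: "P-value <0,05 with a bilateral hypothesis will be considered significant". The sentence before it reads "Variables will be compared between both sub-cohorts (DMP and non-DMP participants". No outcome, family of comparisons or analysis role is named as being inside or outside the rule.

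Three other places widen its possible reach.

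- **Subgroup analysis (5.1).** Subgroups are formed by every patient characteristic in Section 4.2. Then: "Additionally, subgroup analyses will be performed by DMP membership and healthcare utilization". And: "Subgroup analyses cover all study participants as well as analyses of each chronic disease population".
- **Data analysis (5.2).** "Statistical tests depending on normality for the primary and secondary outcomes to compare" introduces two contrasts: responders vs non-responders to the nudge, and DMP vs non-DMP members.
- **Secondary Outcomes (5.2).** The PRO feedback item on understandability, helpfulness and emotional change is described as exploratory, yet it looks for "statistically significant differences in subgroups (see 5.1 and 4.3". Change in PROM and PREM scores per subgroup also points back to 5.1. For value of care the wording is weaker: "For both categorizations the frequency as well as the variation per subgroups (e.g. region, DMP etc.) will be analyzed".

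The protocol gives no order of testing and no error-rate control for these comparisons.

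**The concern.** The second research question (Section 1.2, first secondary objective) asks how PROM and PREM results differ by age, gender, indication, region, utilization and DMP status. The subgroup and DMP comparisons are therefore a main product of the study.

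With one unqualified threshold, a chance difference in one cell of this grid can be reported as significant variation in care or as a DMP difference, in the same terms as a planned main comparison. A reader could not tell the two apart. The single use of the word exploratory does not help, because that item is itself tied to significance.

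**Working it through.** **1. The plan's own figure (Section 2.5).** 200,000 invited × 0.30 responding × 2/3 allowing follow-up × 0.40 completing = 16,000. This reproduces the stated number of complete data sets. If completion is even across sub-cohorts (an assumption), that is 8,000 DMP and 8,000 non-DMP, or 16,000 / 8 = 2,000 per sub-cohort within one disease.

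**2. Number of comparisons per outcome.** Section 4.2 lists nine characteristics: age, gender, type of disease, DMP participation, BMI, education, profession, household size and household income. Section 5.1 adds healthcare utilization, which makes ten; DMP membership is named again but already counted. All participants: 10. Within one disease the disease variable drops out: 9. Total: 10 + 4 × 9 = 46. This takes one test per variable. Region, named in 1.2 and 5.2, is not in the count; it would add 5, giving 51.

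**3. Expected false positives.** If all nulls are true and all 46 are tested at 0.05: 0.05 × 46 = 2.3 per outcome. Correlation does not change this.

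**4. Chance of at least one.** Treating all 46 as independent gives 1 − 0.95^46 = 90.6%. That ignores that the pool contains the four disease populations. A simulation therefore used independent z values for the four disease cohorts, a pooled z equal to their sum divided by 2, a separate test for type of disease, and an assumed common correlation between the other nine variables:

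| Assumed correlation | Chance of at least one false positive |
| --- | --- |
| 0 | 88% |
| 0.3 | 83% |
| 0.5 | 76% |
| 0.7 | 64% |
| 0.8 | 56% to 57% across runs |

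**5. DMP contrast alone.** Four diseases plus their pool, simulated the same way: about 20% per outcome (1 − 0.95^5 = 22.6% if treated as independent). Over an assumed five outcomes: 51% to 68%. Over an assumed eight: 60% to 84%. Each range is for a correlation of 0.7 down to 0 between outcomes.

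**6. Size of difference the threshold can flag.** Detectable difference at 80% power = (1.960 + 0.842) × √(2/n). With n = 8,000 per group: 2.802 × 0.01581 = 0.044 SD. Within one disease, n = 2,000 per group: 0.089 SD.

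**The case against.** The strongest reply is that the text does not order 46 tests for every outcome. The threshold in 5.1 follows the DMP comparison, the subgroup paragraph names no test, and the Data analysis list restricts testing to two contrasts. Value-of-care variation is only to be analysed. Explicit subgroup significance appears once, in the PRO feedback item, and indirectly for PROM and PREM change through the reference to 5.1. This stands: 46 is an upper count, and the percentages apply only where those comparisons are tested.

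A reader might also infer that every outcome falls under the rule. The documents do not support that. The primary endpoint is decided by a 95% confidence interval criterion (4.1 and 5.2), even though 5.2 adds that "The general methodology (see 5.1) will be applied for the analysis of the primary outcomes", and admission risk is handled by prediction models.

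A reader might infer that false DMP differences are near certain. They are not: about 20% per outcome, and 51% to 84% over five to eight assumed outcomes. Nor does the protocol promise a familywise rate of 5%; it states a per-test threshold only.

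Two further replies carry part of the way. Many differences in such a cohort will be real, so calculations under true nulls show only one side. That is fair, but at this sample size p<0.05 also picks out differences too small to matter. And multiplicity is often left to the SAP, which is not at hand. Absence of an adjustment alone would be no finding. Here, however, the protocol states an operative significance rule and attaches significance to an item it calls exploratory. The primary/secondary and main/second labels exist, but they do not restrict which results may be called significant.

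**Conclusion.** The point holds as a fault in a stated rule: 5.1 does not say which comparisons its threshold governs, and 5.2 combines exploratory with statistically significant. Where subgroup comparisons are tested under it and nothing is truly different, expect about 2.3 false positives per outcome and a 57% to 88% chance of at least one. For DMP vs non-DMP in five populations the chance is about 20% per outcome.

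These figures rest on true nulls, one test per variable, four separate disease cohorts of equal size, and an assumed correlation of 0.8 down to 0 between subgroup variables. Where differences are real, the threshold says little about importance, since about 0.044 SD is detectable in the pooled DMP contrast. The primary endpoint's decision rule is not affected.

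**What to change.** - In 5.1, limit formal significance claims to a short named list: the main comparison the protocol already names for a research question (for the third, report opened vs not opened, in 5.2) and one named DMP vs non-DMP contrast for the second, for example the PROPr index score over the four survey periods in all participants. The first question keeps its interval rule.
- The report-opened comparison covers five behaviour dimensions and succeeds on any one. If it carries a formal claim, it needs its own control, for example Holm or 0.05/5 = 0.01 per dimension.
- Label all other DMP, disease-specific and subgroup comparisons exploratory, and report them as estimates with 95% intervals.
- Where p-values are shown for these, apply Benjamini-Hochberg across the whole subgroup family of a research question. Applying it within each outcome only would leave multiplicity across outcomes uncontrolled.
- In 5.2, remove the significance wording from the exploratory PRO feedback item.

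The cost is wording in 5.1 and 5.2 and no new data. The downside is that fewer results may be called significant.
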